### Data integration

Within the process evaluation, data integration will follow a convergent mixed-methods design. Qualitative and quantitative data will be analyzed both interactively and in parallel, depending on the specific evaluation component, and merged during the interpretation stage (20). Integration will focus on identifying consistencies, complementarities, and discrepancies between data sources. From the provider’s perspective, different methodological approaches will be triangulated. An interactive analysis will be conducted in which the provider questionnaire informs the design and focus of subsequent provider interviews, and the insights gained from these interviews will, in turn, guide the development of the focus groups.

### Methods for additional analyses (e.g., subgroup analyses)

#### Quantitative evaluation

Secondary analyses will be done adjusted for the characteristic “rare tumors yes/no,” as described in the inclusion criteria, as well as for the factor “urban/rural,” which arises from the regional structure of the participating CCCs. Planned subgroup analyses will be conducted for the individual CCCs, the type of tumors (rare: yes/no), and the demographic characteristic of urban vs. rural.

#### Process evaluation

No sensitivity analysis is planned for the process evaluation. There is currently no subgroup analysis planned; this decision will be reevaluated during the evaluation process.

#### Health economic evaluation

Sensitivity analyses, for example, relating to different definitions of the intervention costs, are planned for the health economic evaluation. The same subgroups as in the quantitative evaluation are also considered here.

### Methods in analysis to handle protocol non-adherence and any statistical methods to handle missing data

#### Quantitative evaluation

We differentiate between lack of adherence to the intervention and lack of adherence to the evaluation. Adherence to the intervention is part of the evaluation and will be analyzed but not adjusted in the analyses of outcomes. Non-adherence regarding the evaluation will be addressed by incorporating covariates that reflect relevant aspects of non-adherence into the regression models section. Additionally, separate analyses will be conducted for observational groups with varying levels of adherence. Any differences in outcomes between these groups, as well as the potential role of adherence as a predictor of treatment effectiveness, will be transparently analyzed and reported.

Assuming that missing data can be reasonably treated as missing at random, multiple imputation techniques will be employed to minimize the loss of valuable non-missing information that could occur with other methods, such as inadequate listwise deletion. We will use 500 imputation samples, study center, and center status (control vs. intervention) as predictors. Furthermore, we will consider diagnostic classes and measures of disease severity as potential predictors in the imputation model.

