##### Health economic evaluation

Protocol non-adherence and missing data in the health economic evaluation will be handled in line with the approaches described for the quantitative evaluation.

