Additional challenges include the risk of selection bias in patient interviews, as participation may skew toward patients in better health. To mitigate this, the characteristics of interviewed patients will be compared with those of the broader study population. A further limitation is the absence of health insurance claims data for the health economic analysis, as no statutory health insurance providers are part of the project consortium. While alternative data sources on treatment and healthcare utilization will be used, these cannot capture the full spectrum of SHI-related costs at the same quality as claims data. We rely on self-reported data regarding the utilization of outpatient care, medical remedies and medical aids, long-term care, and rehabilitation services. While the FIMA showed promising results in the validation study regarding the accuracy of the reported utilization, self-reports, especially in this highly affected and vulnerable patient group, may suffer from higher attrition, recall bias, and lower accuracy. If sicker patients are less likely to fill in the FIMA questions, this introduces attrition bias in the corresponding cost estimates. Furthermore, we use information from the MTB recommendations and whether these were implemented to quantify costs for medications, instead of data from claimed prescriptions. While the former more accurately reflects exactly which specific treatments were implemented as a result of the MTBs, the latter would cover all SHI-covered medications prescribed to that patient. As such, our medication cost estimate will underestimate the full medication costs. At the same time, incremental cost differences regarding personalized medications can still be calculated. We obtain full inpatient cost data for all patients who are treated at the included university hospitals from the corresponding controlling departments—these are based on the same exports as inpatient claims data. However, as outlined above, there is a considerable share of study participants who are not treated at the university hospital where they were recruited, and the MTBs take place. This hampers the generalizability of inpatient costs to hospital cases outside of the included university hospitals, and as such, the validity of cost-effectiveness results for external patients.

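### Adjusting outcome and cost models for non-adherence to the evaluation, which is known only after enrolment, can bias the intervention effect and recovers no missing data

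*Protocol article*

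**What the plan says.** The relevant text is in the Protocol article, under the methods for protocol non-adherence and missing data (Quantitative evaluation). The article separates two kinds of non-adherence.

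- **To the intervention:** "Adherence to the intervention is part of the evaluation and will be analyzed but not adjusted in the analyses of outcomes".
- **To the evaluation:** "Non-adherence regarding the evaluation will be addressed by incorporating covariates that reflect relevant aspects of non-adherence into the regression models section". It continues: "Additionally, separate analyses will be conducted for observational groups with varying levels of adherence".

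Missing values are a separate step. Multiple imputation is planned under this condition: "Assuming that missing data can be reasonably treated as missing at random". On the imputation model it says: "We will use 500 imputation samples, study center, and center status (control vs. intervention) as predictors". The next sentence adds: "Furthermore, we will consider diagnostic classes and measures of disease severity as potential predictors in the imputation model".

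For the economic analysis, the article says that protocol non-adherence and "missing data in the health economic evaluation will be handled in line with the approaches described for the quantitative evaluation".

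Two other places bear on the point. The Intervention description lists uniform documentation of tumour board decisions and consistent documentation of follow-up and response among the standardised components. The Discussion says of the utilisation questionnaire: "If sicker patients are less likely to fill in the FIMA questions, this introduces attrition bias in the corresponding cost estimates".

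**The concern.** Non-adherence to the evaluation (late or missing forms, unreturned questionnaires, incomplete follow-up) is observed only after the patient has entered the control or intervention condition. Two routes into it are plausible from the article itself. Certified centres document follow-up in a harmonised way, so non-adherence may differ by centre status. Sicker patients may respond less, so it may also differ by prognosis.

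A variable affected by both is a common consequence of exposure and prognosis. Among patients with the same adherence value, intervention and control patients then differ in prognosis even if the groups were alike at enrolment. A model containing that variable attributes part of this difference to the intervention. The separate analyses by adherence level have the same weakness.

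The covariate also does not do the job it is given. If non-adherence means that the outcome is missing, the covariate is constant among patients with an observed outcome and tells the model nothing about the others.

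The article already declines to adjust for adherence to the intervention. It then adjusts for a variable that also arises after enrolment. At stake are the group contrasts in whichever outcome models receive these covariates and, through the carry-over, the cost comparison.

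**Working it through.** The article states no figure on this point, so there is none to reproduce. It gives no non-adherence rate, severity effect or control outcome rate. Only the planned allocation (3,507 intervention, 1,300 control; Sample size section) comes from the article. Every other input below is an assumption.

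**1. No true effect.** Let A be centre status (1 = intervention), S a frailty score, N non-adherence and Y a binary outcome known for everyone.

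- logit P(N=1) = b − 1·A + 1·S
- logit P(Y=1) = a − 0.8·S, so the true odds ratio for A is 1.00

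The constant b sets the control non-adherence rate and a sets the overall outcome rate to 50%. The logistic model of Y on A and N was fitted to the exact cell probabilities, without simulation error.

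| Control non-adherence | Intervention non-adherence | Adjusted OR, S standard normal | Adjusted OR, S binary (30% frail) |
|---|---|---|---|
| 10% | 4% | 0.963 | 0.989 |
| 20% | 9% | 0.935 | 0.980 |
| 30% | 14–15% | 0.913 | 0.972 |
| 40% | 21–22% | 0.897 | 0.967 |
| 50% | 28–30% | 0.888 | 0.963 |

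Without N the odds ratio is 1.000 in every row. An outcome rate of 30% changes the adjusted values by at most 0.004. Simulated runs of the same set-up gave 0.88 to 0.93 with a continuous score and 0.96 to 0.98 with a binary one. With either dependency removed (A or S dropped from the model for N, control non-adherence 30%), the adjusted odds ratio is 1.000.

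**2. A real effect.** One million simulated patients per scenario, 73% intervention, S standard normal, logit P(Y=1) = −0.4 + 0.3·A − S, outcome again known for everyone:

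| Adherence depends on | Non-adherence, control / intervention | Log OR without N | Log OR with N |
|---|---|---|---|
| status and severity | 30% / 16% | 0.252 | 0.151 |
| severity, slope differing by status | 27% / 32% | 0.252 | 0.292 |
| severity only | 30% / 30% | 0.251 | 0.259 |
| status only | 27% / 12% | 0.253 | 0.252 |

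The shift can go either way. In the first row the odds ratio falls from exp(0.252) = 1.29 to exp(0.151) = 1.16; in the second it rises to exp(0.292) = 1.34. In the last two rows it hardly moves.

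**3. Imputation (secondary).** The set-up had 11 centres, four always in the intervention condition and seven switching, with missingness depending on centre, status and severity. Risk differences:

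| Contrast | Full data | Complete cases | Imputed from centre and status |
|---|---|---|---|
| Within centre | 0.0615 | 0.0809 | 0.0810 |
| Marginal | 0.0636 | 0.0823 | 0.0854 |

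Imputing from centre and status alone corrected nothing here. In single-population runs with severity in the imputation model, the full-data result returned: 0.0621 against 0.0622 where complete cases gave 0.0386, and 0.0624 against 0.0624 where complete cases gave 0.1137.

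**The case against.** **The covariates are undefined.** The article does not say which aspects of non-adherence are meant, at what level they are measured, or which regression models receive them. They could be centre-level or baseline correlates, and the primary model under Analysis and anticipated results names only the study arm. This stands as far as it goes: contamination of the primary analysis is not established. It does not remove the point, because the article states a rule rather than leaving a gap, and adherence to follow-up is in the ordinary case known only after enrolment.

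**The bias needs both dependencies.** This also stands. The article supports severity dependence for the utilisation questionnaire, and status dependence for documentation only by inference. It demonstrates both together for no endpoint.

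**Tier 3 is entered by clinical staff.** A reader might infer that the Discussion expects sicker patients to be missing from the primary endpoint. It does not: the sentence is conditional and concerns self-reported utilisation and costs.

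**The imputation model is not closed.** A reader might infer that imputation will rest on centre and status alone and so reproduce the complete-case bias. The article does not support that, because the next sentence says diagnostic classes and severity will be considered, and an article may leave the final list to the analysis plan. Nor does such imputation return exactly the complete-case estimate: centre is the cluster rather than a stated regressor, and the marginal results differ (0.0854 against 0.0823).

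**Conclusion.** The point holds for the covariate rule. Placing evaluation non-adherence in the outcome or cost models can bias the intervention effect and does nothing to recover missing data. It rests on two assumptions: that the covariates are measured after enrolment, and that non-adherence depends on both centre status and prognosis. With only one dependency, the bias is negligible.

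The size cannot be derived from the article. Under the assumed coefficients, a true odds ratio of 1.00 moved to about 0.88 to 0.98. The larger shifts need a continuous frailty score and high control non-adherence, and under other assumptions the shift runs upward. These are illustrations, not forecasts.

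On imputation only a limited statement holds: centre and status alone would not correct severity-related loss, so the predictors that the article names as possible matter. It is not shown that the planned imputation will fail.

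**What to change.** 1. Remove covariates for non-adherence to the evaluation from the main outcome models and, through the carry-over, from the cost models.
2. Report this non-adherence descriptively by centre status. Label any adherence-adjusted or adherence-stratified model exploratory, and define its covariates and when they are measured.
3. In the imputation model, include diagnostic class and severity measures where collected, rather than only considering them. For patient-reported and cost outcomes, add earlier values of the patient-reported measures. Table 3 schedules diagnosis and the patient questionnaires. It names no clinical severity measure, so the one to be used must be identified.

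The first two changes are wording only. The third costs a slightly larger imputation model. A longer predictor list or a sensitivity analysis for data missing not at random would be optional.

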##### Process evaluation

The non-compliance with the protocol will not be handled, as there is no underlying protocol that needs to be followed as part of the data collection process. Instead, a potential non-compliance in the context of the certification process (necessary to achieve the DNPM standard) represents an important outcome within the process evaluation.

##### Health economic evaluation

Protocol non-adherence and missing data in the health economic evaluation will be handled in line with the approaches described for the quantitative evaluation.

## Discussion

The objective of this project is to establish a nationwide, digitally interconnected, interoperable, and patient-centered network for personalized oncology care. This is particularly beneficial for cancer patients, who often require highly individualized treatment strategies.

The study employs a modified stepped-wedge design, which enables a gradual, center-specific transition from standard, non-harmonized PM practices (control condition) to harmonized, quality-assured PM (intervention condition). In contrast to classical stepped-wedge trials, the timing of each center's transition is not randomized but is instead determined by administrative readiness, as marked by the date of certification. This approach accounts for inter-center heterogeneity and allows institutions to implement the intervention at their own pace, making the design both flexible and pragmatic in a real-world healthcare context.

However, the lack of randomization and a distinct, uniform cutoff point for transitioning from control to intervention introduces complexity in the evaluation. The gradual implementation process may lead to variation within the control condition, which could affect comparability across sites and time points. To address this, we will systematically document and analyze this heterogeneity as part of the evaluation strategy. Moreover, as described in the Methods, we will perform several sensitivity analyses to account for the fact that transition is an entire process and not implemented at a certain date in each center.

The study also benefits from a mixed-methods approach, combining quantitative outcome measures with qualitative data from key stakeholders, including patients and healthcare professionals. This methodological diversity supports the generation of robust, context-sensitive insights into the implementation process.

Additional challenges include the risk of selection bias in patient interviews, as participation may skew toward patients in better health. To mitigate this, the characteristics of interviewed patients will be compared with those of the broader study population. A further limitation is the absence of health insurance claims data for the health economic analysis, as no statutory health insurance providers are part of the project consortium. While alternative data sources on treatment and healthcare utilization will be used, these cannot capture the full spectrum of SHI-related costs at the same quality as claims data. We rely on self-reported data regarding the utilization of outpatient care, medical remedies and medical aids, long-term care, and rehabilitation services. While the FIMA showed promising results in the validation study regarding the accuracy of the reported utilization, self-reports, especially in this highly affected and vulnerable patient group, may suffer from higher attrition, recall bias, and lower accuracy. If sicker patients are less likely to fill in the FIMA questions, this introduces attrition bias in the corresponding cost estimates. Furthermore, we use information from the MTB recommendations and whether these were implemented to quantify costs for medications, instead of data from claimed prescriptions. While the former more accurately reflects exactly which specific treatments were implemented as a result of the MTBs, the latter would cover all SHI-covered medications prescribed to that patient. As such, our medication cost estimate will underestimate the full medication costs. At the same time, incremental cost differences regarding personalized medications can still be calculated. We obtain full inpatient cost data for all patients who are treated at the included university hospitals from the corresponding controlling departments—these are based on the same exports as inpatient claims data. However, as outlined above, there is a considerable share of study participants who are not treated at the university hospital where they were recruited, and the MTBs take place. This hampers the generalizability of inpatient costs to hospital cases outside of the included university hospitals, and as such, the validity of cost-effectiveness results for external patients.

Finally, the evaluation must address several implementation-related challenges, including the potential for confusion between elements of the intervention and aspects of the evaluation (e.g., mistaking data collection activities for part of the intervention itself), iterative modifications to the intervention during the study period (which can make it difficult to attribute outcomes to the intervention), and regulatory differences across participating centers (such as varying ethics approval processes and data protection requirements).

Despite these challenges, the study is expected to deliver valuable insights into the processes and outcomes of implementing harmonized personalized medicine in routine cancer care. The findings will inform future implementation efforts and may serve as a foundation for broader research initiatives in this field.

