		Patient satisfaction and quality of life of patients treated in the MTB • Satisfaction • Quality of life	At study enrollment, 2–3 months after enrollment, and 5–6 months after enrollment	• Modified questionnaire instrument based on the PSCC-G instrument • Established questionnaire instruments for disease-specific quality of life, EQ-5D-5L, and EORTC QLQ-C30 *(included in the patient questionnaire)*
		Health economics • QALYs • Total costs (healthcare costs, intervention costs) • ICER	5–6 months after enrollment	• EQ-5D-5L • Modified FIMA questionnaire • Controlling the data of participating university hospitals • Survey of centers *(included in patient questionnaire)*
	Qualitative evaluation	Patient-level survey: • Understanding and attitude toward personalized medicine • Qualitative assessment of the implementation processes • Expectations regarding care provided by the personalized medicine services (ZPMs)/the decentralized personalized medicine (DNPM) • Perceived care before and during treatment with ZPMs/DNPM • Costs incurred in the context of personalized medicine care	At a later stage in the project	Semi-structured interviews with patients
Meso-level and macro-level	Process evaluation (quantitative)	Perspective of staff from centers for personalized medicine (ZPMs): • Degree of standardization of processes • Establishment of new coordination processes at the medical or professional level (e.g., expert committees) • Implementation and structural costs (costs incurred from transitioning to ZPM/DNPM) • Process costs (ongoing costs before ZPM, or of the individual ZPMs) • Exchange/knowledge transfer between ZPM • Exchange of harmonized data • Presence of interconnected data structures (e.g., completeness, quality) • Exchange of harmonized data between the ZPMs • Communication and decision-making structures and processes	• T0: at the time of certification • T1: at an intermediate stage in the project • T2: at a later stage in the project	Quantitative questionnaire based on the certification forms at the center, participation in meetings of the MTB working group, and analysis of the working group’s meeting minutes *(organizational structure and process survey)*

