### Participant timeline

Table 3 shows the participant schedule throughout the intervention period.

**Table 3 T3:** Participant schedule.

Specification of data collected	Participant schedule			
	Enrolment	2–3 months post-enrolment	5–6 months post-enrolment	Close-out
Time point/assessment	T0	T1	T2	T3
Study participation				
Eligibility screen	X			
Informed consent	X			
Allocation	X			
Clinical data collection				
Socio demographics	X			
Diagnose	X	X	X	
(Further) therapies in the last 3 months outside the MTB recommendation	X	X	X	
MTB recommendations		X	X	
Follow-up on MTB recommendations		X	X	
Scheduled end (follow-up completed after 5–6 months)				X
Reason for premature end				X
Patient questionnaire				
Socio demographics	X	X	X	
Living situation	X	X	X	
Financial Situation	X	X	X	
Social support	X	X	X	
EQ-5D-5L (health-related quality of life)	X	X	X	
EORTC QLQ-C30 (disease-related quality of life)	X	X	X	
FIMA (Utilization of health services)	X	X	X	
Patient satisfaction	X	X	X	
Patient interviews				
Understanding, expectations, and attitudes toward PM, perceived care		X	X	

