### Health economic evaluation

In the health economic analysis, treatment costs and intervention costs will be compared with quality-adjusted life years (QALYs) in a cost–utility analysis for both the intervention and control groups and summarized as an incremental cost-effectiveness ratio (ICER). The ICER reflects the relationship between the additional costs incurred through the ZPM (intervention) and the demonstrated benefit in terms of QALYs.

Quality of life will be assessed using the standardized EQ-5D-5L questionnaire at the start of therapy (T2; baseline), at 6 weeks (T3), and at 6 months (T4) after therapy initiation. These data will be translated into quality-adjusted life years. As cost parameters, the analysis will consider all implementation costs related to establishing the ZPMs at the intervention sites, as well as all treatment-related costs associated with PM in both the intervention and control groups. For this purpose, data will be collected from the controlling units of participating institutions that deliver PM, which provide patient-level information on cost coverage by statutory health insurance (SHI).

Since only a portion of patients are treated directly at the respective centers (in some ZPMs, <50%), and because outpatient costs are not centrally documented within hospital controlling systems—making comprehensive cost capture difficult—additional patient-level data will be collected through the following methods:

Patient self-reports on healthcare utilization will be collected based on an adapted version of the FIMA questionnaire, administered at 3 and 6 months after therapy initiation. Costs of implemented MTB recommendations (primary endpoint, Level 3) will be calculated based on the reported pharmaceuticals and therapy modalities (e.g., using data from the Lauer-Taxe drug price database). To account for process and structural costs associated with care delivery in the ZPMs, focus groups with participating centers will be conducted at the beginning of the project. These will identify both the additional costs incurred through the transition to ZPM-based care and the potential cost savings expected as a result of the structural change.

The analysis will be conducted from the perspective of SHI. The findings will be evaluated for their transferability to the broader SHI-insured population. Statistical uncertainty around the ICER will be illustrated and estimated using cost-effectiveness acceptability curves (CEACs).

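### Drug costs are taken only from implemented MTB recommendations, so the total-cost ICER omits other recorded drug therapy that may differ between arms

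*Protocol article*

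**What the plan says.** Table 2 (Outcomes) lists as health economic endpoints QALYs, an ICER and "Total costs (healthcare costs, intervention costs"). The Health economic evaluation under Analysis and anticipated results takes the statutory health insurance perspective. It scopes treatment costs to "all treatment-related costs associated with PM in both the intervention and control groups" and gives the drug-costing rule: "Costs of implemented MTB recommendations (primary endpoint, Level 3) will be calculated based on the reported pharmaceuticals and therapy modalities", with a named drug price database as an example source. The Discussion confirms the rule: "we use information from the MTB recommendations and whether these were implemented to quantify costs for medications, instead of data from claimed prescriptions". It then states that "our medication cost estimate will underestimate the full medication costs", but adds that "incremental cost differences regarding personalized medications can still be calculated".

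Table 3 (Participant timeline) has an item "Further) therapies in the last 3 months outside the MTB recommendation", marked at enrolment, at 2–3 months and at 5–6 months.

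Three other cost sources matter here:
- The Discussion says that complete inpatient costs are obtained for patients treated at the participating university hospitals.
- The Health economic evaluation under Data collection and management says that cancer treatment given elsewhere is approximated from the documented type of therapy and average controlling costs.
- For the rest, the Discussion says: "We rely on self-reported data regarding the utilization of outpatient care, medical remedies and medical aids, long-term care, and rehabilitation services". Drugs are not in that list.

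**The concern.** An ICER from the payer's perspective needs the net change in cost: what the new therapy adds, less what it replaces. The stated rule prices a drug when it comes from an implemented MTB recommendation. No sentence says that drugs outside the recommendation are priced. The plan expects implemented changes (Tier 3) to be more frequent under the intervention. The unpriced part may then be unequal between arms, and an underestimate of level becomes an error in the difference.

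The Discussion discloses the underestimate of level. It does not say that the underestimate may differ by arm, and its reassurance covers the increment in personalized drugs only, which is not the numerator of the ICER. At stake is the incremental cost, and with it the ICER and the acceptability curves. The primary endpoint is not affected.

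**Working it through.** The documents give no drug cost, Tier 3 rate or ICER, so there is no stated figure to reproduce. The check is in two parts.

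**1. Which source could catch a non-MTB drug?**

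| Source | Reaches non-MTB drugs? |
|---|---|
| Medication component | No; implemented MTB recommendations only |
| Inpatient controlling data | Yes, for inpatient care at study hospitals. The analysis section notes that outpatient costs are not centrally held there and that in some centers fewer than half of patients are treated on site |
| Therapy-type approximation for external treatment | Unclear. It uses recorded therapy type, but its averages come from the controlling data |
| Patient self-report | Not on the listed items; the adapted questionnaire is not shown |

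What remains uncovered is mainly outpatient drug therapy outside the MTB recommendation.

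**2. Effect on incremental cost per patient.** Let
- d = between-arm difference in the proportion receiving MTB drug therapy,
- cM = cost of the MTB drug,
- cS = cost of standard drug therapy,
- s = share of the extra MTB-treated patients who would otherwise have had standard drugs (negative if non-MTB therapy rises on balance),
- u = share of cS caught by another source.

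Counted increment: d × (cM − s × u × cS). 
True increment: d × (cM − s × cS). 
Bias = counted − true = **d × s × (1 − u) × cS**. The MTB drug price cancels.

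For d, the 5% and 7% detectable differences in the Sample size section serve as illustrative values. Everything else is assumed: cS = EUR 10,000 or 30,000, with s and u varied.

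| s | u | d = 5% | d = 7% |
|---|---|---|---|
| 0 | any | 0 | 0 |
| 0.5 | 0 | EUR 250–750 | EUR 350–1,050 |
| 1 | 0 | EUR 500–1,500 | EUR 700–2,100 |
| 0.5 | 0.5 | EUR 125–375 | EUR 175–525 |
| 1 | 0.5 | EUR 250–750 | EUR 350–1,050 |
| −0.25 (cS = 10,000 only) | 0 | EUR −125 | EUR −175 |

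For example, 0.05 × 0.5 × 1 × 10,000 = 250, and 0.07 × 1 × 1 × 30,000 = 2,100. In the last row, 0.05 × (−0.25) × 10,000 = −125, which favours the intervention.

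**The case against.** A reader might infer that standard therapy is costed at zero and that the ICER is therefore biased against the intervention. The documents do not support either statement in that form.

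- **Zero cost.** Inpatient therapy at study hospitals is in the controlling data whether or not the MTB recommended it. External cancer treatment is approximated by recorded therapy type, which may reach part of the rest. The gap is limited to what these two sources miss.
- **Direction.** The Eligibility criteria describe patients who have already had guideline therapy or have rare tumors without one, so there may be little standard drug therapy to displace. The article also expects longer survival with targeted therapy, which could add unpriced later therapy in the intervention arm and reverse the sign.
- **Size.** One might set the displaced drug cost at half the MTB drug cost and conclude that the ICER doubles. That factor applies to incremental drug cost only, under full displacement and no capture elsewhere; the ICER also contains inpatient, other care and intervention costs. Nor is Tier 3 a drug endpoint. It includes changed diagnostics, and genetic counseling recommendations count as changes, so a Tier 3 difference cannot simply be multiplied by a drug price.

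It can also be said that the limitation is disclosed, that treatment costs are deliberately scoped to personalized medicine, that sensitivity analyses are planned, and that unit costing belongs in a fuller plan. This carries some weight. But the article does not leave the matter open. It states a costing rule and a reassurance, and both fall short of the total-cost endpoint in Table 2. The only sensitivity analysis it gives as an example concerns the definition of intervention costs.

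**Conclusion.** The point holds in a conditional form. Following the stated rule leaves recorded drug therapy out of total cost when neither controlling data nor the external-treatment approximation captures it. Because implemented MTB therapy is expected to differ by arm, incremental cost can be biased: upward with displacement, not at all without it, downward if intervention patients receive more non-MTB therapy. The size cannot be derived from the documents. The range of EUR 250 to 2,100 per patient rests on assumed drug costs, half to full displacement, no capture elsewhere, and a drug-therapy difference set equal to the 5% to 7% of the Sample size section. It shows scale and is not an estimate. The effect on the ICER depends further on the QALY difference, for which no figure is given. This concerns a secondary endpoint, but it should be corrected because the needed information is largely planned for collection.

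**What to change.** In the Health economic evaluation under Analysis and anticipated results, and in the Discussion:

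1. Price the non-MTB therapies recorded at the 2–3 month and 5–6 month visits in both arms, with the price source used for MTB drugs. Use a standard cost by regimen where amount or duration is not recorded.
2. Count post-enrolment therapy only. The enrolment entry looks back before study entry and must be left out. The three-month look-back at a visit held at two months also reaches one month (3 − 2) before enrolment.
3. Exclude therapy already costed through controlling data or the therapy-type approximation. Reconcile the two Health economic evaluation sections and the Discussion on whether that approximation covers non-MTB drugs.
4. Include the result in total cost and the ICER, and keep the MTB-drug-only cost as a named sensitivity analysis.
5. State in the Discussion that the reassurance about personalized medications does not extend to the total-cost ICER.

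The cost is extra coding and pricing work, with approximate regimen prices where detail is missing. The article does not show how much drug detail the Table 3 item captures, so the precision of this component is uncertain. No new visit or questionnaire is required.
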